### Study procedures and timeline

Figure 2 outlines the flow of participants through the study. Women eligible for the RCT will be directed to the web-program to register, consent and complete T0 baseline measures for the study, following procedures successfully utilised in our previous studies [27]. Randomisation will then occur with participants immediately redirected to their respective homepages. Following baseline assessment, randomisation will occur via an automated computer-program, with participants allocated to either the Intervention condition, or Minimal Intervention Attention-Control condition. Six weeks after enrolment, participants will receive email notification to complete the T1 post-intervention assessment, with T2 and T3 follow-up questionnaire email notifications sent 3 and 6 months later. Non-responders will receive two automated email reminders, and one telephone reminder to complete follow-up assessments.

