### Measures

Table 2 outlines the efficacy outcomes that will be assessed using a battery of validated self-report measures at baseline, post-intervention (primary endpoint), 3-month and 6-month follow-ups, supplemented with website usage data and patient health service use data obtained via data linkage of government databases (‘Services Australia’). Figure 3 outlines the schedule of assessments.

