### Primary analyses

Linear Mixed Models (LMM) will be employed following completion of data collection to examine the efficacy of the intervention, in line with the statistical methodology utilised in previous trials our group has published [27, 28]. Analysis will be by intention to treat, defined as all patients who register. LMM will be used to model all continuous outcomes while accounting for covariance between repeated measures on patients and adjusting for baseline measures, which improves precision of estimation of effects. These models will allow for comparing patterns of change over time by testing group by time interaction, and estimating and testing differences between groups at time points of interest via linear contrasts. Mixed models are valid for data that are missing completely at random and missing at random; patterns of missing data will be considered to assess potential missing data mechanisms. In the present study, the fixed main effects will be treatment condition (intervention, control), and time (post-treatment, 3-month, 6 month), with the baseline measure of the outcome entered as a covariate. A random subject effect will be entered into the model to allow the trajectory of each individual to differ by a constant elevation from the group trajectory. Between-group effect sizes and reliable change indices will be calculated to provide a measure of the magnitude and clinical significance of changes, respectively. No interim analysis is planned.

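### The random-intercept model gives all three visits one residual variance; if correlation with baseline fades and the SD does not fall, the post-intervention SE is too large and the 6-month SE too small

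*Protocol article*

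**What the plan says.** All references are to the protocol article.

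- **Primary analyses** specifies a linear mixed model with treatment, time (three post-baseline visits) and their interaction, "with the baseline measure of the outcome entered as a covariate". A random subject effect is added "to allow the trajectory of each individual to differ by a constant elevation from the group trajectory". The same section speaks of "accounting for covariance between repeated measures on patients and adjusting for baseline measures", but names no random slope, residual covariance structure, robust SE or baseline-by-time term.
- The same model is used for "estimating and testing differences between groups at time points of interest via linear contrasts".
- **Measures** lists assessments "at baseline, post-intervention (primary endpoint), 3-month and 6-month follow-ups". The Abstract sets the superiority criterion at post-treatment, and Hypotheses adds that the effect should persist at 3 and 6 months. Single-visit contrasts therefore carry both the primary and the follow-up claims.
- **Study procedures and timeline** puts the first follow-up six weeks after enrolment, "with T2 and T3 follow-up questionnaire email notifications sent 3 and 6 months later". The visits fall at about 1.5, 4.5 and 7.5 months.
- **Sample size and justification** uses one SD (20) and one within-subject correlation (0.6) for all visits.

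**The concern.** A random intercept with one baseline slope implies equal variance and equal correlation across the follow-up visits. The three visit-specific contrasts then share one pooled residual variance and, with complete data, one SE.

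The visit six weeks after baseline may well be predicted better by the baseline score than the visit about six months after that, particularly in a progressing disease. If so, the residual variance after baseline adjustment is smallest at post-intervention and largest at 6 months. A pooled variance would then overstate the SE at the primary endpoint and understate it at 6 months. At stake are power for the primary test and the error rate of the test behind the claim that the effect lasts.

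**Working it through.** **Inputs from the article:** SD 20; correlation 0.6; one baseline and three follow-up measures; difference 4 points; 147 per group. **Assumed:** two-sided 5% level (not stated, but it reproduces 147), and every decay or SD pattern below.

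**1. The plan's own figure.** The ANCOVA variance factor is (1 + 2×0.6)/3 − 0.6² = 0.3733. Then n = 2(1.960 + 0.842)² × 400 × 0.3733 / 4² = 146.5, so 147 per group. This reproduces.

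**2. Formula.** Let ρ_t be the correlation of visit t with baseline and let SD be 20 throughout. The common slope is b = mean(ρ_t). The true residual variance at visit t is 400(1 − 2bρ_t + b²). The random-intercept model uses the average of the three. SE = √(2 × variance / 147).

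**3. Under the plan's inputs** (0.6 at every visit) the variance is 400 × 0.64 = 256 and the SE is 1.866 at each visit. Model and truth agree. Power for 4 points at one visit is Φ(4/1.866 − 1.960) = 57%.

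**4. With decay averaging 0.6,** the variance is 400(1.36 − 1.2ρ_t). The average is still 256, so the model SE stays at 1.866.

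| Assumed ρ_t (T1/T2/T3) | True variance | True SE | Model/true SE, T1 and T3 | 6-month type I error |
|---|---|---|---|---|
| 0.65/0.60/0.55 (mild) | 232/256/280 | 1.777/1.866/1.952 | 1.05 and 0.96 | 6.1% |
| 0.70/0.60/0.50 (moderate) | 208/256/304 | 1.682/1.866/2.034 | 1.11 and 0.92 | 7.2% |
| 0.75/0.60/0.45 (strong) | 184/256/328 | 1.582/1.866/2.112 | 1.18 and 0.88 | 8.3% |

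For example, under moderate decay the 6-month type I error is 2[1 − Φ(1.960 × 1.866/2.034)] = 2[1 − Φ(1.798)] = 7.2%. At post-intervention the same calculation gives 3.0%, which is conservative.

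**5. Post-intervention power for 4 points.** Random intercept, moderate decay: Φ((4 − 1.960 × 1.866)/1.682) = 58%. With a visit-specific slope and variance the variance is 400(1 − 0.70²) = 204 and the SE 1.666, so power is Φ(4/1.666 − 1.960) = 67%. The same steps give 58% against 62% for mild decay and 59% against 74% for strong decay.

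**6. Simulation check** (REML random-intercept fit, 1,500 replicates; Monte Carlo error about 0.6 points on a 5% rate). Moderate decay used correlations of 0.7 between adjacent follow-up visits.
- Moderate decay, complete data: SE ratios 1.07 (T1) and 0.93 (T3); 6-month type I error 7.5%.
- Moderate decay, 185 per group, about 20% dropout missing at random: 1.13 and 0.90; 8.4%.
- Decay only among follow-up visits, baseline correlation flat at 0.6: ratios 1.03/1.00/1.03, so no distortion of note.
- Moderate decay with SD falling to 19 and then 17 at the last two visits: ratio 1.01 at 6 months, type I error 5.2%. At the 3-month visit the ratio was 0.94.

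**7. Unequal SDs in closed form.** Variance at t is s_t² − 2cρ_t s_t + c², where c = mean(ρ_t s_t). For correlations 0.70/0.60/0.50:
- SD 20/18.5/17: c = 11.2; variances 211.8/219.0/224.0; 6-month type I error 5.3%; post-intervention power 64% against 67%.
- SD 20/22/24 (stress case): c = 13.07; variances 204.9/309.8/433.1; model SE 2.07 against true 1.67 (T1) and 2.43 (T3); 6-month type I error about 9%; post-intervention power 48% against 67%.

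**The case against.** **The article may not be the whole specification.** It never says the random intercept is the only covariance component, and an unseen analysis plan could add a residual structure. That is possible. But the article goes beyond naming a mixed model. It states what the random effect does, and that statement describes a constant shift for each woman. A stated structure can be reviewed as stated.

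**The plan is consistent with itself.** One correlation and one SD match the equal-correlation model, and under them nothing is lost. This stands. The point is sensitivity to an assumption, and the article contains no contradiction here.

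**The trigger is undocumented.** Nothing in the article reports fading correlation or growing spread. The outcome is bounded at 0 to 100, and the SD could fall if the sickest women drop out, which can cancel the 6-month error. This also stands and limits the claim to a conditional one.

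**Stronger readings a reader might infer, which the documents do not support:**
- That the primary test is invalid. Under decay without a falling SD it is conservative.
- That any decay in correlation causes the problem. Decay confined to the follow-up visits does not. The condition is unequal residual variance after baseline adjustment.
- That the random intercept is why post-intervention power is only about 58%. The plan's own inputs already give 57% for a single visit, because 147 per group is sized for the average of three. The random intercept forgoes a gain that would exist if early correlation were higher.
- That 48% power and 9% type I error are to be expected. They need an SD rising to 24, for which the article has no source.

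**Conclusion.** The point holds as a conditional one. The stated model is right if the planning assumptions of equal correlation and equal SD are right. It misstates visit-specific precision if correlation with baseline fades and the SD does not fall. For mild to strong assumed decay at SD 20, the SE is 5 to 18% too large at post-intervention and 4 to 12% too small at 6 months. Mild to moderate decay costs roughly 4 to 9 percentage points of power at the primary endpoint and puts 6-month type I error at about 6 to 7%, or about 8% with dropout under moderate decay. The effect is modest, and only the follow-up claim is exposed to false positives. The change is worth making because it is nearly free and protects both contrasts.

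**What to change.** In Primary analyses, replace the random subject intercept with an unstructured covariance over the three post-baseline visits. Include baseline-by-time as well as group-by-time, and use Kenward-Roger degrees of freedom. Name the fallback for non-convergence in advance, for example heterogeneous Toeplitz and then compound symmetry with robust SEs. With complete data this reproduces a separate ANCOVA at each visit.

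The cost is a change of wording and of model code. It adds four covariance parameters (six instead of two) and two baseline-by-time terms, which is negligible with about 300 women (370 × 0.8 = 296). If compound symmetry does hold, nothing material is lost.

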### Secondary analyses

#### Health economics

Within-trial incremental costs associated with the intervention when compared to the control will be estimated using Medicare Benefits Schedule (MBS), Pharmaceutical Benefits Scheme (PBS) and Australian Refined Diagnosis Related Groups (AR-DRG) data. Costs related to the intervention itself will be determined from administrative data collected as part of the trial. The primary health economics outcome will be the incremental cost per unit change in the EORTC QLQ-C30 mental functioning subscale, while the secondary outcome will be the incremental cost per quality adjusted life year (QALY) gained. Within-trial cost-effectiveness with respect to both outcomes will be analysed, allowing for bivariate uncertainty with bootstrapping of participant costs and effects to maintain the covariance structure. To estimate QALY gains, participants will complete the EQ-5D-5L instrument at each assessment. Patient-level measures of utility derived from the EQ-5D-5L instrument will be integrated with survival curves using the quality-adjusted survival analysis (QASA) method. This analysis will include cost-effectiveness, acceptability, net benefit and expected net loss curves to inform decision makers of the optimal strategy at any given threshold for different patient subgroups. Sensitivity analysis will include estimating the incremental cost per unit change in the number of practitioners seen in the previous 3 months based on health services data (via Services Australia data linkage). Of note, given that FMW-A encourages help-seeking, increases in health service utilisation may be observed in a subset of participants; this will be explored qualitatively.

#### Qualitative interview data

Qualitative interview data will be analysed using thematic analysis to identify salient themes in participants’ experience of using the web-based intervention.

### Compliance with regulatory guidelines

The study will be conducted in full conformance with principles of the “Declaration of Helsinki”, Good Clinical Practice (GCP), the Australian National Statement on Ethical Conduct in Human Research (NHMRC, 2007), Australian Code for the Responsible Conduct of Research (2007) and with the laws and regulations of Australia. All study documentation has received ethical approval from the Southern Adelaide Clinical Human Research Ethics Committee (SAC-HREC 2021/HRE00407). Site Specific Assessment (SSA) approval will be sought and obtained from local research governance offices of all participating sites. During the study, the CIA will submit documents recording any serious adverse events or any amendments to this protocol to SAC-HREC. At the conclusion of the study, the CIA will notify SAC-HREC that the study has ended by submitting a final report.

## Discussion

Digital health tools offer one means of addressing the significant access barriers experienced by women with metastatic breast cancer, where symptom burden or physical incapacity, social or geographic isolation, or financial strain preclude participation in face-to-face therapy. However, no RCT has been published to date on the efficacy of a digital health program for this population. While digital health solutions have proliferated in the general community, none have been specifically developed for women with MBC, thus lack the required essential evidence of efficacy, safety, acceptability, accessibility, and content-relevance for this vulnerable population [31]; RCTs of population specific interventions are, therefore, critical. To our knowledge, *Finding My Way-Advanced* is unique in addressing this research and resource gap.

The large-scale nature of this national multi-site RCT will enable examination of the *efficacy* of the program in improving mental and overall quality of life, reducing distress including fear of progression, unmet needs, and health service use. Furthermore, this study offers the opportunity to evaluate potential *moderators* of change and determine how they overlap or differ to those identified in our earlier *Finding My Way* program for those treated with curative intent [44]. This information has clinical utility in aiding healthcare professionals in identifying for whom and under what conditions digital health is beneficial, and who may be better suited to other modalities.

If the intervention efficacy is evidenced, this program has individual, system-level, national and international significance. For individuals, the program provides an accessible and cost-effective method of obtaining therapeutic benefits. By improving mental QOL and distress, the overall burden of their disease is reduced via potentially reducing their severity of side effects/toxicities [6, 7], and increase ability to tolerate treatments [8], while increasing capacity for valued activities. This in turn has the potential for system-level benefits, via reduced health service utilisation / health system burden [9].

Nationally, the already developed and approved implementation and dissemination plan will ensure immediate and ongoing population-level scaling of *Finding My Way-Advanced* in Australia via the national body, BCNA. There is also strong potential for international scaling, as demonstrated by our group’s prior history of trialling adaptations of the original *Finding My Way* digital health program in the USA [45] and the UK [46], and a commitment to conduct a replication study of FMW-A in the UK is already in place, funding-dependent. This program is readily and directly scalable to the English-speaking world, and can form a foundation for culturally-appropriate adaptations and translation to other languages or settings. Finally, FMW-A provides a template for delivering psychological treatment for individuals diagnosed with other metastatic cancers, or chronic health conditions that face similar physical incapacity, social isolation and/or financial strains and access barriers.

In summary, this study is significant in providing an innovative method for providing psychological treatment for a high-need but underserved population, while evaluating the benefits to the health-system and patients. It brings strong methodological rigour to the research design, will provide important contributions to the digital health evidence-base and, most importantly, addresses the recognised paucity of psychological interventions developed specifically for women with MBC.

## Data Availability

The datasets generated during and/or analysed during the current study are available from the corresponding author on reasonable request. We cannot obtain ethical approval to place clinical trial data on a public repository, due to the highly confidential / sensitive nature of the data, which participants have not consented to be released.

## Abbreviations

ACT: Australian Capital Territory
ANCOVA: Analysis of Covariance
AR-DRGs: Australian Refined Diagnosis Related Groups
BCNA: Breast Cancer Network Australia
CBT: cognitive behaviour therapy
FMW-A: Finding My Way – Advanced
ID code: identification code
LMM: linear mixed models
MBC: metastatic breast cancer
MBS: Medicare Benefits Schedule
MQOL: mental quality of life
NSW: New South Wales
PBS: Pharmaceutical Benefits Scheme
QALY: quality adjusted life years
QOL: quality of life
RCT: randomised controlled trial
SAC-HREC: Southern Adelaide Clinical Human Research Ethics Committee
